### 4.2. Data Collection

The test will be conducted by members of the PEFP research group, who have no competing interests, and details of the intervention group allocation will not be available to the testers. Before the test, two training sessions will be conducted to ensure the quality of the test, which will be conducted by professionals from the test equipment company. The workshop will (1) cover the development characteristics and special needs of young children; and (2) deliver the basic concepts, testing skills, and emergency plans for young children.

### 4.3. Data Management

All research data entry will be carried out by two people, followed by an interrater consistency check. Consent forms will be stored separately from participant data, and a unique identifier code will be assigned to each participant. Data will be deleted immediately from voice recorders after the transcription, with pseudonyms used in all reports in place of participants’ names. Data will only be accessible to primary researchers and statisticians after application to the research group. Data will be stored for a maximum of 5 years before being securely destroyed.

All phases of this study will be monitored by a data safety officer, who has worked for monitoring data collection and data analysis. The data safety officer is responsible for the data management and distribution of applied data, and will not obtain the details of the research. Management of the trial data will be in accordance with the data management plan, which was developed and approved by the project group. Moreover, the data will be published in two ways: writing academic papers and uploading to the experiment registration website.

### 4.4. Data Analysis Plan

Baseline characteristics and unadjusted study outcome measures will be summarized by intervention groups using descriptive statistics and used to assess between-group equivalence at baseline. Prespecified baseline covariates in both primary and secondary outcome analyses will include age, sex, FMSs capacity, PF level, and PA level.

Baseline demographic descriptors and primary and secondary outcome measures will be compared across groups by using analysis of variance (a non-parametric test will be used when the data does not conform with a normal distribution) for continuous variables and the χ^2^ test for categorical variables. The planned descriptive data on measured-point FMSs and PF will be tabulated across the intervention groups and control group. In our primary analysis of the FMSs and PF outcome, we will use mixed model analyses to estimate the differences with their corresponding 95% CIs, comparing the BA, RA, BM, and MA groups with the control group. Time, physical exercise programs (intervention or control groups), and their interaction will be fixed factors. The random effects will be the kindergarten and individual to take into account the clustered data structure.

Multilevel linear regression models will be constructed to assess the effectiveness of the physical exercises on FMSs and PF performance. The baseline data of the outcome variables, assessment points, intervention groups, and any imbalanced covariance will be added to the model along with the kindergartens and PA as random effects. The interaction between physical exercise and FMSs and PF will be tested.

Secondary analyses will investigate the effect of the intervention on other domains using different types of regression analyses, depending on the outcomes. Logistic regressive analyses will be constructed to assess the interference factors. The models will be used to assess the effect of forms of physical exercise, and to explore associations between secondary outcome measures, and will be adjusted for various confounding factors (e.g., sex, PA).

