## 4. Statistical Analysis

### 4.1. Sample Size

The primary outcome variables in this study are FMSs and PF. Before recruitment, a priori power analysis was performed in G*Power 3.1 to calculate the sample size necessary to detect meaningful changes from the baseline to the post-intervention time points in the total raw scores of seven FMSs (i.e., 10-m shuttle-run, hopping, bouncing a ball, jamming coins, kicking, balance beam, and one-leg stand) and seven PF (i.e., balance beam, handgrip, standing long jump, sit-and-reach, 10-m shuttle running, 20-m shuttle running, handgrip strength, and hopping). Using an alpha of 0.05 and a power of 80%, the calculation of the power to detect a pre-post change in these measures was based on the effect sizes reported in a recent systematic review. The expected effect size of the intervention on FMSs and PF was at 1.42 and 0.36 (standardized mean difference, SMD), respectively [51]. With reference to these results, a prudent estimation of the effect size (SMD = 0.36) was used for the calculation. The required sample was calculated to be 70. To account for the clustering effect, this number was then multiplied by a design effect (DE) of 1 + (*m* − 1) × ICC, where *m* is the average cluster size and ICC was estimated at 0.05. With an estimated average class size of 30, at least 150 participants will have to be recruited. Based on previous studies, we presumed a drop-out rate of 15%, implying a minimal sample size of 150/0.85 = 176 children in total. This study takes the class as the cluster of random sampling; the class size in recruited kindergartens is 30–35. Therefore, considering the drop-out rate and special samples (preschool children with developmental retardation or hyperactivity disorder), each experimental group was divided into two classes, implying about 60 children in each group. The total size is 300.

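### Section 4.4 compares the five arms by ANOVA, a rank test or chi-square with no allowance for clustering; the p-values are invalid, though the primary mixed model is a separate analysis

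*Protocol article*

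**What the plan says.** Section 4.4 (Data Analysis Plan) opens with descriptive summaries by arm, to be "used to assess between-group equivalence at baseline". The next paragraph states: "Baseline demographic descriptors and primary and secondary outcome measures will be compared across groups by using analysis of variance". For measurements that fail normality, the section allows a substitute: "a non-parametric test will be used when the data does not conform with a normal distribution". Categorical data go to a chi-square test. It mentions no cluster term or adjustment for any of these tests.

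The same section then plans a mixed model for the primary comparison of each intervention with control, with kindergarten and individual as random effects. It also plans multilevel models to which covariates found imbalanced will be added. It prespecifies age, sex, FMSs, PF and PA at baseline as covariates, but gives no rule for calling any other covariate imbalanced.

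The design is clustered throughout. Section 4.1 (Sample Size) applies a design effect, and there the "ICC was estimated at 0.05" for an average class size of 30. The unit is not consistent, however. Sections 2.1 and 4.1 make it the class, with two classes and about 60 children per arm. Section 2.3 assigns recruited kindergartens to the five groups, and section 2.1 names five kindergartens, so that version gives one per arm.

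**The concern.** One-way ANOVA, the usual rank test for several groups and Pearson's chi-square all require independent observations. Children in one class or kindergarten share teachers, facilities and intake, and the plan accepts this by assuming a positive ICC and by putting a random effect in its main model. The comparisons quoted above drop that allowance. The variance of an arm mean is then understated, and the tests reject too often when nothing differs.

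Two uses are at stake:

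- **Outcomes.** If the sentence covers outcomes after baseline, unadjusted p-values between arms would stand beside the mixed-model results and could contradict them.
- **Baseline.** If it covers baseline only, the p-values would be read as evidence for or against equivalence. A significant result would overstate the evidence, and a non-significant one would not show equivalence even with a correct test. The results may also decide which additional covariates enter the multilevel model, making that model depend on the data.

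**Working it through.** **Inputs**
- Arms: 5 (section 2.1). Children: about 60 per arm, 300 in total (section 4.1).
- ICC 0.05, alpha 0.05, class size 30 (section 4.1).
- Layout A, class as unit: 2 clusters of 30 per arm (sections 2.1 and 4.1).
- Layout B, kindergarten as unit: 1 cluster of 60 per arm (sections 2.1 and 2.3).
- Assumption: the ICC of 0.05 applies to the variable tested and, in layout B, to the kindergarten. The document gives no ICC by variable or for kindergartens.

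The plan states no error rate for these tests, so there is no figure of its own to reproduce. Its sample-size step from 70 to 150 does not follow from its design effect (70 × 2.45 = 171.5), but that is a separate matter and does not enter here.

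**Design effect**, by the plan's formula 1 + (m − 1) × ICC:
- A: 1 + 29 × 0.05 = 2.45
- B: 1 + 59 × 0.05 = 3.95

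**What the F statistic does under no difference** (total variance 1)
- The between-arm mean square has expectation equal to the design effect.
- The within-arm mean square has 300 − 5 = 295 df. In A it pools 290 df within classes at 0.95 and 5 df between classes within arm at 2.45: (290 × 0.95 + 5 × 2.45)/295 = 287.75/295 = 0.975. In B it is 0.95.
- The F ratio is therefore inflated by about 2.45/0.975 = 2.51 in A and 3.95/0.95 = 4.16 in B.
- The 5% critical value of F(4, 295) is 2.40. Dividing by the inflation gives 0.956 in A and 0.578 in B. The chance that F(4, 295) exceeds these is about 43% and 68%.

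Drawing from the exact null distribution (1,000,000 draws) gives 43.1% and 67.9%. Full simulation of the planned tests (20,000 trials each) agrees:

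| Test, ICC 0.05 | A: 2 × 30 per arm | B: 1 × 60 per arm |
|---|---|---|
| ANOVA | 44% | 68% |
| Kruskal-Wallis | 41% | 66% |
| Chi-square (true proportion 0.5) | 43% | 68% |

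Changing to the rank test or to chi-square therefore does not help.

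**Sensitivity to the ICC (ANOVA)**

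| ICC | A | B |
|---|---|---|
| 0.01 | 12% | 20% |
| 0.02 | 20% | 37% |
| 0.05 | 43% | 68% |
| 0.10 | 67% | 87% |

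**Sensitivity to cluster size at ICC 0.05:** 2 × 25 gives 38% and 2 × 35 gives 49%; 1 × 51 gives 63% and 1 × 70 gives 73%.

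**Control check.** In layout A an F test on the ten class means, with 4 and 5 df, rejects 5.0% of the time, so the excess comes from ignoring the clusters. In layout B five clusters in five arms leave 5 − 5 = 0 error df, and no valid cluster-level test exists.

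**The case against.** The strongest reply is that these tests are peripheral. Baseline can be read as governing the whole sentence. The preceding paragraph is about baseline summaries, the sentence that follows says the FMS and PF data at each measurement point will be tabulated, and the comparisons of interventions with control are then assigned to a mixed model with a kindergarten random effect. A reader might infer from the quoted sentence that ANOVA is the trial's effectiveness analysis. The document does not support that; the sentence is ambiguous and the primary analysis is stated separately.

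A reader might also infer that these tests define equivalence and select the model covariates. The text ties equivalence to descriptive statistics and never says that a significant test makes a covariate imbalanced. What remains is that it offers no other criterion, so the tests may well serve as one. Age, sex, FMSs, PF and PA are adjusted for in any case.

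Nor can 43% to 68% be read as the share of all comparisons that would be falsely significant. The two figures belong to two incompatible randomisation units, and both apply one ICC to every variable. Some variables, sex for example, may cluster less. The limitations section suggests yet another layout, with a control group in the same school as each intervention group, which neither calculation represents.

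Finally, a chance difference between clusters at baseline is a real difference in the children enrolled. The better objection at baseline is to significance testing and data-driven adjustment as such, with the inflated error rate making both worse.

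These points limit the reach of the concern. They do not make the named tests valid for a cluster-randomised trial.

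**Conclusion.** The concern holds in limited form. Whichever way the sentence is read, section 4.4 specifies between-arm tests that assume independent children in a trial that randomises clusters. Given the plan's ICC of 0.05 for the variable tested, the true level of a nominal 5% ANOVA is about 43% if classes are randomised and about 68% if kindergartens are. At ICC 0.01 it is still about 12% or 20%. Such p-values support no statement about baseline equivalence or about outcome differences. This defect does not reach the primary FMS and PF analysis. An influence on the covariates of the multilevel model is possible but not stated. The change should be made; it is not one on which the primary result depends.

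**What to change.** In section 4.4:

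1. Delete the ANOVA, rank and chi-square comparisons between arms.
2. Report means and SDs, or counts, by arm and time point without p-values.
3. Adjust only for the covariates already prespecified (age, sex, FMSs, PF, PA), and drop the addition of covariates found imbalanced.
4. Take inference between arms only from the model whose cluster random effect matches the unit randomised.

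Step 4 first requires the class of sections 2.1 and 4.1 to be reconciled with the kindergarten of section 2.3. If there is one kindergarten per arm, no model can separate arm from kindergarten, and the mixed model does not rescue the comparison.

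Steps 1 to 3 change wording only and leave fewer tests to run; they need no extra data. Reconciling the unit is a matter of wording if classes were in fact randomised. If kindergartens were, it exposes a design problem that goes beyond this point.

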## Abstract

**Background**: Evidence shows that physical exercise promotes preschoolers’ fundamental movement skills (FMSs) and physical fitness (PF). However, studies that assess the effectiveness of different types of physical exercise interventions to improve FMSs and PF in preschool children remain scarce. To explore and compare the effectiveness of different physical exercise on FMSs and PF, interventions comprising ball games (BGs), rhythm activities (RAs), basic movements (BMs), and a combination of all related activities (multiple activities, MAs) will be conducted among preschoolers. **Methods**: A single-blind, five-arm, cluster-randomized trial will be conducted in kindergarten in Shanghai, China. In total, 300 healthy preschoolers, aged 4 to 5 years, will be randomized to four intervention groups (BG, RA, BM, or MA) and one control group (unorganized physical activities). Four intervention groups will receive three 30-min lessons weekly for 16 weeks. At the baseline, the end of the 16-week intervention, and the 6-month follow-up after the end of the intervention, the primary outcomes (FMSs and PF) and physical activity (PA), and sociodemographic and anthropometric data will be assessed. **Discussion**: This study will provide vital information regarding the effect of different physical exercise interventions on preschool children’s FMSs and PF, PA, and the potential interactions between these domains. The most effective intervention strategy can be generalized to kindergarten and other preschool educational institutions in practice to promote preschoolers’ development of FMSs and PF. **Conclusions**: This study protocol aims to provide a method to solve the problem of “how to arrange physical exercise and which kind of physical exercise program can promote FMS and PF better in preschool children”.

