
In China, young children (3–6 years old) population is 57 million, 81.7% of whom were enrolled in kindergarten in 2018. Children spend approximately 40 h each week in kindergarten [36]. However, there is little empirical evidence showing the effect of physical exercise on preschoolers’ FMSs and PF in China. Above all, the present trial is designed to respond to the theoretical and evidence gap. Therefore, the aims of this trial are to (1) determine the effectiveness of each of these physical exercise interventions in improving preschool children’s FMSs and PF; and (2) establish the differences between the effectiveness of different physical exercise programs on preschool children’s FMSs and PF. The research hypothesis is that physical exercise interventions will improve children’s FMSs and PF more than unorganized activities, and that MA will show larger beneficial effects than BA, RA, or BM on children’s FMSs and PF.

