## 2. Methods

### 2.1. Study Design

The study is a single-blind, cluster-RCT study, with the kindergarten class as the cluster for the intervention. This study is a part of the Physical Exercise on FMSs and PF of preschoolers (PEFP) project. The PEFP project is a series of studies, including a cross-sectional survey (covering six provincial and municipal regions in China) and the aforementioned RCT (implemented in Putuo District, Shanghai, China). Preschoolers recruited from 5 kindergartens will be cluster-randomly allocated to 5 groups (i.e., four intervention groups and one control group). The intervention groups are (1) the BG group, consisting of football, basketball games, etc.; (2) the RA group, including cheerleading, rhythm exercise, etc.; (3) the BM group, consisting of different basic movements, such as walking, running, jumping, climbing, throwing, catching, etc.; and (4) the MA group, combination of all kinds of physical exercise that have been used in other intervention studies. The control group (control) is an unorganized PA group (Figure 1). The content of the intervention comes from previous research combined with consultation and interviews with preschool educators [7,37].

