#### 3.3.1. Primary Outcome Measures

The primary outcomes in this study are FMSs and PF.

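### The primary analysis specifies only programme-versus-control comparisons, so aim 2 and the hypothesis that MA beats the other programmes have no specified contrast

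*Protocol article*

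**What the plan says.** Section 1 (Background) sets two aims. The first is the effectiveness of each programme. The second is to "establish the differences between the effectiveness of different physical exercise programs". The hypothesis has two matching parts: the programmes beat unorganised activity, and "MA will show larger beneficial effects than BA, RA, or BM". The arm called BG elsewhere is written BA here and in section 4.4.

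The Abstract looks ahead to a choice among programmes: "The most effective intervention strategy can be generalized to kindergarten and other preschool educational institutions". Section 8 (Conclusions) puts the trial's question as which kind of programme works better.

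Section 2.1 has "5 groups (i.e., four intervention groups and one control group". Section 3.3.1 states: "The primary outcomes in this study are FMSs and PF".

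For the primary analysis, section 4.4 plans "mixed model analyses to estimate the differences with their corresponding 95% CIs", and names the differences: "comparing the BA, RA, BM, and MA groups with the control group". Time, programme and their interaction are fixed factors. Two further passages of section 4.4 mention programmes: multilevel regressions of the effectiveness of the exercises, and secondary models of the effect of forms of exercise. Neither names a pair of programmes to be compared.

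Section 4.1 gives the error rate for the sample size: "Using an alpha of 0.05 and a power of 80" per cent. That calculation targets a pre-post change.

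**The concern.** The primary analysis answers aim 1 only. The second half of the hypothesis, and the aim that justifies four active arms, have no prespecified contrast.

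Four comparisons with control cannot fill the gap. One programme may differ significantly from control and another may not, while the two hardly differ from each other. If the contrasts are left open until the data are seen, the choice of which programmes to compare becomes post hoc. A recommendation on which programme kindergartens should adopt could then rest on no direct comparison.

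A smaller matter is that two primary outcomes and four contrasts give eight tests, and the article states no rule for combining them.

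**Working it through.** **1. What is asked and what is specified.** Contrasts per outcome:

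| Source | Contrasts | Specified in section 4.4? |
|---|---|---|
| Aim 1; hypothesis, first part | BG, RA, BM, MA each versus control (4) | Yes |
| Hypothesis, second part | MA-BG, MA-RA, MA-BM (3) | No |
| Rest of aim 2 | BG-RA, BG-BM, RA-BM (3) | No |

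Five arms give 5 × 4 / 2 = 10 pairs, of which the primary analysis names 4.

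**2. Why comparisons with control do not answer aim 2.** With control effect C, (MA − C) − (BG − C) = MA − BG. With equal arms, MA − BG has the same standard error as each comparison with control, so its z value is z(MA vs C) − z(BG vs C). If one z lies just above 1.96 and the other just below, the first programme is declared effective and the second is not, yet the z for their difference is near 0.

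**3. Precision of one between-programme contrast.** The plan gives no figure for such a contrast, so there is none to reproduce. Inputs from section 4.1 are about 60 children per arm, ICC 0.05, average class size 30 and SMD 0.36. The last is the plan's planning value, used here only as a yardstick for a difference between programmes.

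- Design effect: 1 + (30 − 1) × 0.05 = 2.45. (Separately, 70 × 2.45 = 171.5, not the 150 in section 4.1. Nothing below uses the 150.)
- Effective number per arm: 60 / 2.45 = 24.5.
- SE in SD units: √(2 / 24.5) = 0.286.
- Half-width of the 95% CI: 1.96 × 0.286 = 0.56 SD.
- Power at two-sided 0.05: Φ(0.36 / 0.286 − 1.96) = Φ(−0.70) = 24%. Ignoring clustering it would be 50.5%.
- With 15% dropout (60 × 0.85 = 51 per arm): 21%.
- If the true difference is half as large (0.18): 9%. If it were as large as the plan's FMS value of 1.42: 99.9%.
- For 80% power at SMD 0.36: 122 per arm unclustered, 299 with the design effect, 352 with dropout.

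The normal approximation is generous with two classes per arm, so true power would be lower.

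**4. Error rate of the eight planned tests (side point).** Assumptions: no true effects, every test read at two-sided 0.05, valid standard errors, equal arms sharing one control. The correlation r between the two outcomes is not in the document and is varied.

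- Eight independent tests: 1 − 0.95^8 = 33.7%.
- With the shared control (400,000 simulated trials):

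| r | Chance of at least one false claim |
|---|---|
| 0 | 28.7% |
| 0.3 | 28.0% |
| 0.5 | 26.9% |
| 0.7 | 24.9% |
| 0.9 | 21.2% |

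Balance beam, 10-m shuttle run and hopping are in both batteries (sections 3.3.1 and 4.1, Tables 2 and 3), so r near 0 is implausible and the lower part of the range is more likely.

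**The case against.** The strongest reply is that nothing is lost. Programme and programme-by-time are already fixed effects, and if programme has five levels, as the four named comparisons imply, every pairwise contrast can be taken from the fitted model. This stands. A reader might infer that the plan makes it impossible to test MA against the others, or rules it out; the document does not support that. It supports only that no such test is specified.

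The other text in section 4.4 does not close the gap. The analysis of variance across groups opens with baseline descriptors. Even if read as covering post-intervention outcomes, it is an omnibus test with no cluster term, and would not show that MA beats each alternative.

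A second reply is that multiplicity control is commonly left to an SAP, which is not shown. This largely stands. The 0.05 is an input to the sample size and section 4.4 promises estimates with 95% CIs, so reading each test at 0.05 is an inference. Multiplicity is therefore only a side point. A reader might also count the six MA contrasts over both outcomes and quote an error rate for 14 tests. That rate would not describe this plan, which does not contain those six tests.

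Third, the plan nowhere says that programmes will be ranked by their result against control. That is true: the Abstract implies a choice but gives no rule. The risk comes from the missing rule.

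**Conclusion.** The point holds in this form: section 4.4 limits the primary contrasts to each programme against control, while section 1 makes between-programme differences an aim and MA superiority a hypothesis, and no section specifies a between-programme contrast. This is a mismatch within the article and does not depend on what an SAP might add.

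The direct contrasts will be imprecise: about ±0.56 SD, and about 24% power at SMD 0.36. Both figures rest on the plan's own ICC, class size and 60 per arm. The side point is a 21-29% chance of at least one false claim over the eight planned tests, conditional on each being read at 0.05 and on the assumed outcome correlation of 0.9 to 0.

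**What to change.** **Change to section 4.4.**

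- State that programme enters the primary mixed model as a five-level factor.
- Prespecify MA-BG, MA-RA and MA-BM at the end of the 16-week intervention, for FMSs and for PF, each with a 95% CI.
- Report BG-RA, BG-BM and RA-BM from the same model with 95% CIs, to complete aim 2 if MA is not best.
- Base any statement that a programme is most effective on these direct contrasts, not on rank against control.
- State one multiplicity procedure, for example alpha 0.025 per outcome with Holm over the contrasts used for claims. With the four control contrasts and three MA contrasts, the first step is 0.025 / 7 = 0.00357. If the other three pairs are also to support claims, they join the family and the first step is 0.025 / 10 = 0.0025.
- Use BG throughout in place of BA.

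**Cost.** The change is to analysis wording, with no new data. The price is low power: about 24% per contrast at SMD 0.36 and alpha 0.05, and about 5% at 0.00357. The plan should say that a non-significant contrast is not evidence that two programmes are equivalent.

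**What it does not cure.** Sections 2.1 and 2.3 describe five kindergartens and assignment by kindergarten to five groups, while section 4.1 takes the class as cluster with two classes per group. If each arm is one kindergarten, programme is confounded with kindergarten, and added contrasts cannot separate them.

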### 2.3. Randomization and Masking

First, the information of the recruited kindergarten will be obtained, including the name of classes, and the number of children in each class. Then, an opaque envelope will be used for simple random assignment, and recruited kindergartens as a unit will be randomly assigned to one of five groups. The generation of the random assignment will be completed by the main person who is in charge of the intervention. As this is a behavioral and skill-specific intervention, eligible children in the same class will receive an identical strategy to avoid confounding influences, such as different exercise instruments or teachers. Furthermore, details of the intervention group allocation will not be available to participants and their teachers. Data analysts will not include blind processing, which will be performed by two separate individuals for statistical analysis of the research results. Participants and teachers will be unblinded when the research is finished by providing a simple report and brochure to the kindergarten.

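### The class is the named cluster and is sized for, but neither model in 4.4 has a class term; type I error per contrast is about 21% if the ICC of 0.05 applies to change

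*Protocol article*

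**What the plan says.** Section 2.1 describes a cluster-randomised trial "with the kindergarten class as the cluster for the intervention". Section 4.1 repeats this: "This study takes the class as the cluster of random sampling; the class size in recruited kindergartens is 30–35". It applies a design effect with an average class size of 30 and an ICC of 0.05, and then states that "each experimental group was divided into two classes, implying about 60 children in each group". Section 2.3 adds that "eligible children in the same class will receive an identical strategy", giving shared instruments and teachers as the reason. Under 3.2.1, kindergarten teachers deliver the lessons.

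The primary model in 4.4 is specified in two sentences: "Time, physical exercise programs (intervention or control groups), and their interaction will be fixed factors", and "The random effects will be the kindergarten and individual to take into account the clustered data structure". The second, multilevel model in 4.4 adjusts for the baseline outcome and takes kindergartens and PA as random effects. Class appears in neither.

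The randomised unit is itself described in more than one way. Section 2.3 says that "recruited kindergartens as a unit will be randomly assigned to one of five groups", and section 2.1 says "Preschoolers recruited from 5 kindergartens will be cluster-randomly allocated to 5 groups". Section 7 instead places a control group in the same school as each intervention group.

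**The concern.** Children in one class share a teacher and 16 weeks of lessons between the first two assessments, so their changes from baseline are likely to be correlated. The sample size allows for that correlation and the stated analysis does not.

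The gap matters most for the time-by-programme interaction, which is the test of effect. A kindergarten intercept and a child intercept are the same at both visits and drop out of change from baseline. What remains is child-level residual variance, as if children had been randomised one by one. Class-level variation in change then looks like a programme effect. With two classes per arm, one strong teacher could make a programme appear effective, and the abstract intends the most effective programme to be taken up by kindergartens generally.

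**Working it through.** **Inputs.** From 4.1: m = 30 per class, ICC = 0.05, two classes and about 60 children per arm, alpha 0.05 (taken as two-sided, in line with the 95% CIs in 4.4). From 4.4: the fixed and random effects, read as random intercepts. Not in the article: how any class variance divides between a part constant over time and a class-by-time part.

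**1. The plan's own figure.** The design effect is DE = 1 + (30 − 1) × 0.05 = 2.45, and 70 × 2.45 = 171.5. The article gives 150, so its figure does not reproduce. That is a separate point, and the planned 300 exceeds either number. What matters here is that class clustering was meant to be allowed for. The article states no type I error under its model.

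**2. Error when class variation in the tested quantity is ignored.** Standard errors are too small by a factor of √DE = √2.45 = 1.57. The error is 2[1 − Φ(1.96/√DE)] = 2[1 − Φ(1.96/1.57)] ≈ 0.21.

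| ICC of change (m = 30) | DE | Error per contrast |
|---|---|---|
| 0.01 | 1.29 | 8.4% |
| 0.02 | 1.58 | 11.9% |
| 0.05 | 2.45 | 21% |
| 0.10 | 3.90 | 32.1% |

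At ICC 0.05 the error is 18.9% for m = 25.5 (30 less 15% drop-out) and 23.3% for m = 35.

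**3. Which part of the class variance counts.** Only the class-by-time part survives in change. Take total variance 1 at each visit and a constant child component of 0.5 (an assumption). The ICC of change is then class-by-time variance divided by class-by-time plus residual variance. Null simulations of the group-by-time test with two visits, one kindergarten per arm and 20,000 runs gave:

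- class variance 0.05, all constant over time: 5.3%;
- class-by-time 0.025, residual 0.475, so ICC of change 0.025/0.50 = 0.05: 21.4%;
- class-by-time 0.05, residual 0.45, so ICC of change 0.05/0.50 = 0.10: 33.5%.

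The layout hardly alters this test. With class-by-time ICC 0.05, a further simulation (4,000 runs × 4 contrasts) gave 21.9% (two visits) and 21.3% (three) with one kindergarten per arm, and 21.1% and 21.6% with arms spread across kindergartens.

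**4. A post-score comparison with a kindergarten intercept.** This approximates the second model. With classes randomised across five kindergartens, a single-time simulation without the baseline covariate gave 18.7% (class variance 0.05, kindergarten 0), 15.3% (0.025 and 0.025) and 10.5% (0.01 and 0.04). The kindergarten term absorbs part of the class variance, but not all.

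**5. Does a class-level analysis repair it?** A t test on class means of change, with 10 − 5 = 5 df, ran at 4.8% to 5.2% when there was no kindergarten-by-time variance. Normal quantiles on the same class means gave 10.5%. With one kindergarten per arm and kindergarten-by-time variance 0.025 beside class-by-time 0.025, the child-level test ran at 41.4% and the class-level t test still at about 14%.

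**The case against.** Three objections deserve weight.

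*The size is conditional.* A reader might infer that the primary tests simply run at 21%. The article does not support that. Section 4.1 does not say whether 0.05 refers to scores at one visit or to change, and if class effects are constant over time the error stays near 5%. This objection stands and sets the form of the conclusion. It does not remove the defect: full constancy is hard to assume when each class has its own teacher-led lessons between the assessments, and an ICC of change of only 0.01 already gives about 8%.

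*The kindergarten may be the right level.* Section 2.3 randomises kindergartens, and a random effect at the randomised level is the usual choice. That is fair, but five kindergartens in five arms leave the kindergarten effect aliased with arm, so its variance cannot be estimated. A reader might also infer that adding a class term would then make the intervals valid; step 5 shows that it would not.

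*An article condenses.* Detail may properly sit in an analysis plan that is not shown. Here, however, the article states the random effects, and they conflict with its own design and sample-size sections.

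**Conclusion.** The point holds as a contradiction within the article: the cluster it names and sizes for is absent from the random effects of both models. Standard errors for the programme contrasts are too small whenever classes differ in how much their children change.

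The type I error per contrast is about 21% if the ICC of 0.05 applies to change with 30 per class. It ranges from near 5% (class effects constant over time) to about 33% (all of the 0.05 is class-by-time, with a constant child component of half the total variance). For a post-score model with classes randomised within kindergartens, about 10% to 19% is the better guide. None of the calculations includes the baseline covariates listed in 4.4. The contradiction is certain; the size is not, because the article does not give the variance split or settle the randomised unit.

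**What to change.** 1. Reconcile sections 2.1, 2.3, 4.1, 4.4 and 7 on whether the class or the kindergarten is randomised and whether arms share a kindergarten. The random effects cannot be settled before this.
2. If classes are randomised, add a class random effect with a class-by-time term, or analyse the 16-week score adjusted for baseline with a class random intercept. Use small-sample degrees of freedom (Kenward-Roger or Satterthwaite) that match the layout. Ten classes in five arms without kindergarten blocks leave 10 − 5 = 5. Five fixed kindergarten blocks leave about 10 − 1 − 4 − 4 = 1, so blocking and 5 df cannot both be had.
3. If each arm is one kindergarten, no random-effect term removes the aliasing. Still include the class term, state that the intervals do not cover kindergarten-level variation, and limit the conclusions accordingly.

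The cost is wording in 4.4 plus wider intervals and less favourable power. At an ICC of change of 0.05 with 5 df (t quantile 2.57), intervals widen by about 1.57 × 2.57/1.96 = 2.1 times. Under item 3 the limit on the conclusions is a real loss that analysis wording cannot recover.
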